## **Version date:** February 27, 2022

## **Summary of the project**

| Study title | Mainz Immunoadsorption Study in Adults with Post-COVID (IAMPOCO) |
| --- | --- |
| Applic | [name], MD |
| Study location | Main |
| Fund | Third-party funding (Diamed Medizintechnik, Cologne, Germany) |
| Study design/type | Prospective randomized single-blind placebo-controlled study |
| Number of subjects | 40 subjects |
| Study population | Adults recruited from participants in the Gutenberg Post-COVID Study who had at least one positive SARS-CoV-2 PCR test at least 6 months prior to study inclusion, as well as new or persistent symptoms of SARS-CoV-2 infection 3 months after a positive PCR test that have persisted for at least 2 months. |
| Planned start of study | March 8, 2023 |
| Study duration per subject | 4.5 |
| Planned study duration | Recruitment period: 6 months  Duration of the clinical study: 18 months |
| Primary endpoint | Effectiveness of immunoadsorption on symptom burden in patients with post-COVID syndrome as measured by the values of:   - Post-COVID-19 Functional Status Scale (PCFS) - Chalder Fatigue Scale - Montreal Cognitive Assessment (MOCA) - MFI-20 - Bell Score - Strength measurement   And their comparison before and after verum therapy and before and after sham therapy (before therapy cycle 1/after therapy cycle 1 and before therapy cycle 2/after therapy cycle 2) |
| Secondary endpoints | 1. Frequency of adverse events under active and sham treatment  2. Prevalence of anti-adrenergic and anti-muscarinic autoantibodies in patients with post-COVID syndrome:   - Proportion of subjects with evidence of anti-α1-adrenoreceptor AK - Proportion of subjects with evidence of anti-α2-adrenergic receptor antibodies - Proportion of subjects with evidence of anti-β1-adrenoreceptor AK - Proportion of subjects with evidence of anti-β2-adrenoreceptor AK - Proportion of subjects with evidence of anti-β3-adrenoreceptor AK - Proportion of subjects with evidence of anti-M1 acetylcholine receptor AK - Proportion of subjects with evidence of anti-M2 acetylcholine receptor AK - Proportion of subjects with evidence of anti-M3 acetylcholine receptor AK - Proportion of subjects with evidence of anti-M4 acetylcholine receptor AK  1. Concentration of:  - Anti-α1 adrenoreceptor AK - Anti-α2-adrenoreceptor AK - Anti-β1 adrenoreceptor AK - Anti-β1 adrenoreceptor AK - Anti-β1-adrenoreceptor AK - Anti-M1 acetylcholine receptor AK - Anti-M2 acetylcholine receptor AK - Anti-M3 acetylcholine receptor AK - Anti-M4 acetylcholine receptor AK   Before and after treatment with active substance and placebo (before therapy cycle 1/after therapy cycle 1 and before therapy cycle 2/after therapy cycle 2) |
| Safety parameters | Not applicable |

## 3.4 Funding

- Diamed GmbH, Cologne, Germany
- Treatment, inpatient stay, and experimental analyses are financed by the clinic's own funds.
- For detailed analyses such as RNAseq and proteome analyses, it is planned to obtain additional third-party funding where possible.

## 3.5 Registration in a publicly accessible study registry

Planned at clinicaltrials.gov

## **Scientific background**

Long or post-COVID refers to a syndrome of symptoms that develop three months after a suspected or confirmed infection with SARS-COV-2, have developed within the three months, or are still present from the acute infection and persist for at least two months.^1^ The type of symptoms does not play a role in the definition of post-COVID syndrome to date.^1, 2^ The prevalence of post-COVID syndrome is estimated at 43% of all SARS-COV-2 infected individuals, with hospitalized patients suffering from persistent symptoms more frequently (54%) than non-hospitalized patients (32%).^3^ Women are more likely to suffer from post-COVID syndromes, with a prevalence of 49%, than men, who are affected in 32% of cases of persistent or newly occurring symptoms after COVID-19, according to .^3^ The most common symptoms are fatigue (23% of those affected), memory problems (14%), dyspnea (13%), sleep disorders (11%), and joint pain (10%).^3^ Headaches, myalgia, anxiety, and depression are also frequently reported.^3^

In terms of the type, variety, and duration of symptoms, post-COVID resembles a clinical picture observed after various viral infections, such as the Epstein-Barr virus, the herpes simplex virus, or the influenza virus, namely myalgic encephalomyelitis and chronic fatigue syndrome (ME/CFS).^4, 5^ Here, too, patients mainly suffer from fatigue, concentration and memory problems, and non-restorative sleep.^4, 5^ Some authors see post-COVID as a form of ME/CFS triggered by SARS-COV-2 infection or the immune response to the infection.^5^

The possible pathomechanisms suspected to be behind these syndromes are diverse. However, the pathogenesis and underlying causes are not yet fully understood.^6^ Similarly, the causes of post-COVID syndrome are still unclear.^4^ Both clinical pictures are thought to involve autoimmune mechanisms triggered by the body's response to infection and sustained by the similarity of the body's own proteins to pathogen components (molecular mimicry).^7In^the context of this autoimmunity, antibodies against the body's own structures may also be formed, such as antinuclear antibodies, which target components of the cell nucleus.^7^ In patients suffering from ME/CFS, antibodies against α- and β-adrenergic receptors and against muscarinic acetylcholine receptors, among others, have been detected.^8^ No correlations between antibody concentrations and the severity of the disease or the clinical picture of ME/CFS could be demonstrated, nor are these antibodies specific or sensitive for ME/CFS.^8, 9^

With the detection of autoantibodies in patients with ME/CFS, forms of therapy that specifically target the formation of autoantibodies have also been investigated. For example, two randomized controlled trials involving 30 and 151 ME/CFS patients investigated B-cell-depleting therapy with the anti-CD-19 antibody rituximab versus placebo. The results showed no significant improvement in fatigue symptoms compared to placebo, although a reduction in B-cell concentration was achieved.^10, 11^ In the primary endpoints (improvement in fatigue symptoms after 3 months and after 24 months), there was no significant difference between placebo and rituximab therapy in either study.^10, 11^

Immunoadsorption is another therapeutic option for reducing the concentration of autoantibodies. In this procedure, the patient's blood is first separated into cellular components and plasma, and then the plasma is passed through adsorbents.^12^ The adsorbents have specific surfaces for binding different classes of immunoglobulins, so that the plasma is then largely purified of immunoglobulins and thus also of autoantibodies and returned to the patient together with the cellular components.^12^ This reduces the concentration of immunoglobulins and thus also the concentration of autoantibodies. ^12, 13^ Immunoadsorption is one of the established treatment options for many antibody-mediated autoimmune diseases.^14^

## **5. Project objectives**

- To examine the effects of immunoadsorption therapy on symptom burden in patients suffering from post-COVID symptoms
- Objective assessment of post-COVID symptoms using standardized tests and questionnaires
- To determine the prevalence of autoantibodies against alpha- and beta-adrenergic adrenoreceptors and muscarinic acetylcholine receptors, as well as possible correlations with certain post-COVID symptoms or their severity
- Verification of the effects of immunoadsorption therapy on the concentrations of autoantibodies against alpha- and beta-adrenergic adrenoreceptors and muscarinic acetylcholine receptors

## **6. Target parameters**

6.1 Primary endpoints:

Effectiveness of immunoadsorption on symptom burden in patients with post-COVID syndrome measured by the values of:

- Post-COVID-19 functional status scale (PCFS)
- Chalder Fatigue Scale
- Montreal Cognitive Assessment (MOCA)
- MFI-20
- Bell Score
- Strength measurement

and comparison before and after active treatment and before and after sham treatment (before treatment cycle 1/after treatment cycle 1 and before treatment cycle 2/after treatment cycle 2).

6.2 Secondary endpoints:

- Frequency of adverse events under active and sham treatment
- Prevalence of anti-adrenergic and anti-muscarinic autoantibodies in patients with post-COVID syndrome:
  - Proportion of subjects with evidence of anti-α1-adrenoreceptor Abs
  - Proportion of subjects with evidence of anti-α2-adrenergic receptor Abs
  - Proportion of subjects with evidence of anti-β1-adrenoreceptor Abs
  - Proportion of subjects with evidence of anti-β2-adrenergic receptor Abs
  - Proportion of subjects with evidence of anti-β3-adrenoreceptor Abs
  - Proportion of subjects with evidence of anti-M1 acetylcholine receptor Abs
  - Proportion of subjects with evidence of anti-M2 acetylcholine receptor Abs
  - Proportion of subjects with evidence of anti-M3 acetylcholine receptor Abs
  - Proportion of subjects with evidence of anti-M4 acetylcholine receptor Abs
- Concentration of:
  - Anti-α1-adrenoreceptor Abs
  - Anti-α2-adrenoreceptor Abs
  - Anti-β1-adrenoreceptor Abs
  - Anti-β1 adrenoreceptor Abs
  - Anti-β1 adrenoreceptor Abs
  - Anti-M1 acetylcholine receptor Abs
  - Anti-M2 acetylcholine receptor Abs
  - Anti-M3 acetylcholine receptor Abs
  - Anti-M4 acetylcholine receptor Abs

Before and after active and sham treatment (before therapy cycle 1/after therapy cycle 1 and before therapy cycle 2/after therapy cycle 2).

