## **Study population**

### 8.1 Inclusion criteria:

- Fulfilment of the WHO diagnostic criteria for post-COVID syndrome
- Written consent to participate in the study
- Previous participation in the Gutenberg Post-COVID study
- Minimum age of 18
- PCFS score of at least 2

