## **Biometrics**

In a published post-COVID cohort from Germany (Lier et al., Frontiers Neurol 2022, DOI: 10.3389/fneur.2022.988359), the median MoCA score was 27 with a interquartile range of 25 to 28. The null hypothesis is that immunoadsorption cannot reduce the score by 2 points, i.e., below the MoCA threshold. To achieve a power of 90%, according to a calculation using the G*Power Version 3.1.9.7 utility program (Faul et al., Behav Res Methods 2009), two treatment groups of 19 subjects each are required (effect size 1.0, one-sided Wilcoxon Mann-Whitney test with alpha level 0.05 and 1:1 randomization). To account for possible dropouts, the number of cases is set at 2x 20 subjects.

1. **Data management and data protection**

- Laboratory parameters will be collected. In addition, patients will complete questionnaires that allow conclusions to be drawn about their quality of life, symptom burden, cognitive abilities, and resilience in everyday life.
- Medical examinations will be carried out to assess lung function, strength, central and peripheral nervous system function, heart rhythm, and vital signs.
- Patient data and other information about blood samples and the findings of the above-mentioned examinations will be archived in a pseudonymized, password-protected database.
- The data and samples can therefore only be traced back using a key that is accessible only to the study director and the medical director of the First Medical Clinic. The data is labeled with the same key as the samples. The requirements of medical confidentiality and data protection are therefore ensured within the framework of this study.
- The data will not be passed on to third parties. The data will be stored for 10 years.
  - The data will be stored in pseudonymized form.
  - Consent can be revoked at any time in writing or verbally without giving reasons.

1. **Handling of biomaterials**

- Patient data and other information about the blood samples and the examination findings will be archived in pseudonymized form in a computerized database.

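### Six unranked primary endpoints have no success rule, and the only stated hypothesis, alpha and sample size are for one of them, MoCA

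*Protocol*

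**What the plan says.** Section 6.1 (repeated in the project summary) describes the primary endpoint as "Effectiveness of immunoadsorption on symptom burden in patients with post-COVID syndrome measured by the values of" PCFS, the Chalder Fatigue Scale, MoCA, MFI-20, the Bell Score and strength. It adds the contrast: "and comparison before and after active treatment and before and after sham treatment", over both cycles. The six are a plain list with no order, no lead endpoint and no statement of how many must be positive.

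The Biometrics section deals with MoCA only. It cites a cohort in which "the median MoCA score was 27 with a interquartile range of 25 to 28" and continues: "The null hypothesis is that immunoadsorption cannot reduce the score by 2 points, i.e., below the MoCA threshold". The sample size follows: "To achieve a power of 90"% the plan finds that "two treatment groups of 19 subjects each are required" ("effect size 1.0, one-sided Wilcoxon Mann-Whitney test with alpha level 0.05 and 1:1 randomization"), raised to 2 x 20 for dropouts. This is the only alpha in the protocol, and all of it goes to MoCA. The section does not call MoCA the lead or confirmatory endpoint, and it gives no hypothesis, alpha or power for the other five.

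Two other places bear on the list. Section 8.1 selects patients on function ("PCFS score of at least 2"), with no cognitive criterion. Item 2 of the amendments restricts the study's neurological examinations to a pain rating and MoCA, while the procedures section places the strength measurement among the neurological examinations.

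**The concern.** The protocol does not fix what would count as a positive trial. With six primary endpoints and no rule, a favourable result on any one could be reported as the primary endpoint having been met. The same data could also be called negative by a reader who expected all six, or MoCA, to succeed.

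The sample size does not settle the matter. It suits MoCA tested alone or first, yet nothing in the text gives MoCA that place. The instruments closest to the symptom-burden objective (PCFS, Chalder, MFI-20, Bell) have no stated power. At stake are the false positive rate under one reading and the power under the others.

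**Working it through.** **Inputs from the protocol.** Six primary endpoints (section 6.1). One-sided alpha 0.05, effect size d = 1.0, 1:1 allocation, Wilcoxon-Mann-Whitney test, 90% power and 19 per group (Biometrics), all for MoCA.

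**Input not in the protocol.** The correlation between endpoints. I assume a common value and show a range.

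**1. The plan's own figure.** Scale n by the Wilcoxon efficiency for normal data, 3/π = 0.955, then use the one-sided noncentral t distribution.
- At n = 19: effective n = 19 × 0.955 = 18.14; df = 2 × 18.14 − 2 = 34.3; noncentrality = 1.0 × √(18.14/2) = 3.01; critical t = 1.69; power = 90.4%.
- At n = 18 power is 89.0%, so 19 is the smallest sufficient number. The stated figure reproduces.

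**2. Reading A: any one positive at one-sided 0.05 is enough.**
- Six independent endpoints: 1 − 0.95^6 = 26.5%.
- Five independent endpoints (strength removed): 1 − 0.95^5 = 22.6%.
- For correlated endpoints, I simulated equicorrelated normal test statistics (1,000,000 draws per value):

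| Assumed correlation | Six endpoints | Five endpoints |
|---|---|---|
| 0 | 26.5% | 22.6% |
| 0.3 | 22% | 19% |
| 0.5 | 19% | 17% |
| 0.7 | 15% | 13% |
| 0.9 | 10% | 9% |

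**3. Reading B: all six must be positive.** The error under the global null cannot exceed the 5% of a single test. Power is the cost. With d = 1.0 on every endpoint and 19 per group, it is 0.904^6 = about 55% if the endpoints are independent, and about 63%, 69% and 75% at correlations of 0.3, 0.5 and 0.7.

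**4. Reading C: alpha is shared or ordered.** Same method, d = 1.0, 19 per group:
- Single endpoint, or first in a fixed sequence, one-sided 0.05: 90%.
- Single endpoint, two-sided 0.05: 83% (90% needs 24 per group).
- Strictest step of a six-way Holm or Bonferroni split, one-sided 0.05/6 = 0.0083: 69% (90% needs 30 per group).

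The stated 19 per group and 90% power therefore fit only one endpoint tested alone, or first in sequence, at one-sided 0.05. All these figures use the plan's own parallel two-group test and its d = 1.0.

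**The case against.** The strongest reply is that multiplicity procedures are commonly left to a statistical analysis plan, which is not at hand. A fixed sequence starting with MoCA would fit the stated sample size exactly. That is fair, and the missing adjustment method is not in itself a finding. But the set of primary endpoints and the endpoint that sizes the trial are both fixed in this protocol, and the protocol does not connect them.

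A reader might infer that each of the six is to be tested at one-sided 0.05 and that the false positive rate is therefore 26.5%. The protocol does not say this. The level appears once, for MoCA, and no rule says that a single positive result suffices. Independence is also the upper case. Chalder, Bell and MFI-20 all measure fatigue, so positive correlation is likely, and at 0.9 the figure is about 10%. The count may be five rather than six. The error rates therefore stand only as conditional figures.

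A reader might also infer that MoCA is unusable because a median of 27 leaves little room below its cap of 30. The documents do not support that. They give no MoCA values for patients selected on PCFS. Even under an assumed normal distribution matched to the cited quartiles (mean 26.6, SD 2.22, rounded, capped at 30), the cap shortens a 2-point gain to about 1.7 but also narrows the spread. Power at 19 per group falls only from about 85% to 83–84%. The ceiling is no part of this point.

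**Conclusion.** The point holds in conditional form. The protocol names six unranked primary endpoints without a success rule, and gives a hypothesis, alpha and sample size for MoCA only. The arithmetic for MoCA is correct; the fault lies in the link between the endpoint list and the sample size.

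If any one positive at one-sided 0.05 counts, the familywise error is two to five times the nominal 5%, depending on the assumed correlation. If all must succeed, the error is controlled but power is well below 90%. Which of these applies cannot be read from the protocol, and that is the defect. It should be corrected before the data are analysed, because it decides what the trial can conclude.

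**What to change.** 1. In section 6.1 and the project summary, either name one confirmatory primary endpoint that matches the symptom-burden objective and make the others secondary, or keep them all as primary and state how the familywise error is controlled (a fixed sequence with its order, or Holm). Which instrument leads, and whether the test is one- or two-sided, are for the sponsor to choose and state.
2. Reconcile the list with amendment item 2: say whether strength is still measured and still primary.
3. In Biometrics, restate the power or detectable effect for the chosen endpoint and alpha.

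**Cost.** This is amendment wording. Fewer endpoints can be called confirmatory, and the stated power may fall: at d = 1.0 and 19 per group it is about 90% for one endpoint at one-sided 0.05, 83% at two-sided 0.05, and 69% at the strictest step of a six-way one-sided Holm split. Regaining 90% in the last two cases would take 24 or 30 per group against the planned 20, and section 9.6 describes treatment capacity as limited. The fix does not require more patients; restating the figure honestly is enough.

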## **Study design**

The Mainz immunoadsorption study in adults with post-COVID is a single-center, randomized, controlled, single-blind study with a cross-over design that aims to investigate the potential effect of immunoadsorption therapy on symptom burden in people with post-COVID. The study is being conducted by an interdisciplinary team of investigators.

Included subjects are first randomized to receive either 5 verum treatments (immunoadsorption with TR-350 adsorber) or 5 sham treatments (connection to the Plasauto Sigma without adsorber). All subjects will receive both the real treatment and the sham treatment unless they decide against the respective therapy cycle before the start of the respective therapy cycle. Randomization is only used to determine which treatment is given first.

Participating subjects may withdraw from the study at any time, including after the first therapy cycle or before the second therapy cycle.

The subjects are blinded because they do not know whether the treatment is being carried out with or without an adsorber, and it is also not apparent to the subjects, as the TR-350 adsorber and Plasauto Sigma are set up behind a curtain that is not visible to the patient and remain there throughout the treatment.

The blinding of the subjects serves to assess the actual effect of the therapy without the influence of the therapy arm on the patients' reports. Since the therapeutic effects in the present study are predominantly measured using self-report instruments, such an approach seems essential to minimize the influence of distortions caused by psychological effects of the verum therapy on the study results.

[figure not shown]

1 Figure Study design and flow chart

## **Study population**

### 8.1 Inclusion criteria:

- Fulfilment of the WHO diagnostic criteria for post-COVID syndrome
- Written consent to participate in the study
- Previous participation in the Gutenberg Post-COVID study
- Minimum age of 18
- PCFS score of at least 2

### 8.2 Exclusion criteria:

- Psychiatric diagnosis
- Allergy to adsorbent materials, materials used in the tube systems, or substances used for immunoadsorption
- Pregnancy
- Medical contraindications to immunoadsorption, such as severe blood clotting disorders or immunodeficiency syndromes
- Existing antibody-mediated autoimmune disease

### 8.3 Recruitment

The subjects will be recruited from the 700 participants in the Gutenberg Post Covid Study. Patients who meet the criteria for post-COVID will be offered participation in the immunoadsorption study in adults with post-COVID.

### 8.4 Number of participants

### A total of 40 subjects are to be included.

## **Study procedure**

### Information and consent

All participants will be informed in a personal meeting, both by means of a written information sheet and in a detailed discussion, about the objectives of the study, the study procedure, the examinations required as part of the study, the active treatment, the sham treatment, and the associated risks and potential benefits of participating in the study. Furthermore, detailed information will be provided about the data collected during the study, how it will be anonymized, and for what purposes the data will be stored. Study participants will also be informed about the preservation of biomaterials obtained during their participation in the study. Any questions the participants may have will be clarified in a personal interview. After a reflection period of at least 24 hours, written consent is then obtained. Consent given once can be revoked at any time during participation in the study without any disadvantages for the participant.

### Collection of data and procurement of biomaterials

Since the test subjects are recruited from participants in the Gutenberg Long COVID Study, a lot of data is already available from surveys conducted as part of that study. When participating in the Gutenberg Long COVID Study, the subjects were already examined by an interdisciplinary team of doctors from preventive cardiology, preventive medicine, and the Neuroimaging Center at Mainz University Medical Center, so that a wide range of laboratory values and examination findings are already available for each participant, which can be used as baseline values. Standardized questionnaires were handed out, personal interviews were conducted, medical physical examinations were performed, and imaging techniques were used. Many of the values required from blood and urine tests were also already determined when participants were included in the Gutenberg Long COVID study.

